#### Secondary outcome measures

Secondary outcomes comprise the following:

##### Emotional dysregulation

Emotional dysregulation will be quantified with the validation in Spanish of the Emotional Regulation Difficulties Scale (DERS) (70). The original scale has 36 items with a Likert response format of 5 positions (from 1 = almost never, to 5 = almost always) and a structure of six factors: (1) Impulse control difficulties (6 items: “When I’m upset, I lose control over my behavior,” for example); (2) Limited access to emotion regulation strategies (8 items: “When I’m upset, I believe there is nothing I can do to make myself feel better,” for example); (3) Nonacceptance of emotional responses (6 items: “When I’m upset, I feel ashamed at myself for feeling that way,” for example); (4) Difficulty engaging in Goal-directed behavior (5 items: “When I’m upset, I have difficulty concentrating,” for example); (5) Lack of emotional awareness (6 reverse-scored items: “I am attentive to my feelings,” for example) and (6) Lack of emotional clarity (5 items: “I am confused about how I feel,” for example). The DERS has previously been used in pre-post intervention studies as a state variable of emotional dysregulation to assess effectiveness (71–74). This variable will be considered and analyzed as a quantitative variable.

##### Engagement with the app

Engagement will be determined by three parameters: acceptability, subjective use, and objective use. For acceptability, the User Experience Questionnaire will be used in its short version (UEQ-s) (75). The UEQ-s scale contains 8 items that evaluate the app’s pragmatic qualities (attractiveness, clarity and reliability) and hedonic qualities (novel, stimulating). Each item is scored on a Likert scale from 0 to 7, with antagonistic qualities being found at their extremes (0 and 7). Subjective use will be assessed with 5 directed questions are asked with the possibility of a dichotomous response (Yes/No); (“Did you use the app when you were in crisis?”; “In case you used it, was it useful for crisis management?”; “Did you use the app outside of times of crisis? crisis?”; “Do you consider that this modality “out of crisis” helped you to prevent the appearance of new crises?”; “Would you recommend the application to other people?”).

Objective use of the app will be obtained and recorded *via* the participant’s phone number. Specifically, use will be recorded when at least one of the following features of CALMA is used during the study period: opened a “Tips,” arrived at the “Emergency Card,” finished a crisis (due to success or abandonment), opened a notification, added a contact, reviewed their “Moments,” added a picture or content to their “Moments,” closed the app while it was in crisis and ended a crisis successfully. In addition, patients will be defined as “users” of the app if they met the following criteria: subjectively reported using the app in the survey and used at least one feature recorded by our objective measures. Finally, the relationship between the content of the app used by the participants and the primary outcome will be evaluated.

##### Time to psychiatric admission

At follow-ups and at the final interview, participants will be asked if they have had a psychiatric hospitalization for a self-injurious behavior during the follow-up period. This measure will be used to compare time to psychiatric admission in those participants who received the intervention with those participants who did not receive the app.

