### Patient eligibility

#### Subjects

Patients aged 10 to 19 who attend on as outpatient basis or have been hospitalized in Mental Health Services and who have a smartphone where the application can be installed and used are eligible to participate in the study. In addition, participants must have had suicidal behavior in the 4 weeks before entering the study. The SITBI assessment questions will be used to define suicidal behavior: suicide attempt [“made a suicide attempt (i.e., purposefully hurt yourself with at least some intent to die)?”], exhibited a suicidal gesture (Have you ever done something to lead someone to believe that you wanted to kill yourself when you really had no intention of doing so?) or self-injurious behavior (Have you ever done something with the purpose of hurting yourself without wanting to die?–for example, cutting or burning-) in the last month before entering the study (53, 54).

The participant must have plans to continue treatment in the next 3 months, have the ability to provide assent/consent for cognitive or language reasons, and the functional capacity to use the application, which will be operationally determined by a score above 30 on the Self-Care motor domain, above 10 on the Communication cognitive domain and above 14 on the Cognitive domain of Social Knowledge in the Functional Independence Measurement scale (46).

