### Outcomes measures

#### Primary outcome measure

Suicidal behavior will be assessed using the Spanish version of the Self-Injurious Thoughts and Behaviors Interview (SITBI) (68, 69). This is a structured interview consisting of 169 items divided into 5 modules that examine the presence, frequency and characteristics of 5 types of self-injurious behavior: (a) suicidal ideation; (b) suicide plans; (c) suicidal gestures; (d) suicide attempts and (e) self-harm. The SITBI conceptualizes suicide risk on a continuum, starting with suicidal ideation (“thoughts of killing yourself?”), possibly accompanied by a suicide plan [“think about how you might kill yourself (e.g., taking pills, shooting yourself) or work out a plan of how to kill yourself?”] and in some cases by suicide attempt [“made a suicide attempt (i.e., purposefully hurt yourself with at least some intent to die)?”]. The construction of the questions in the original SITBI is consistent with the commonly accepted definitions of each type of behavior. The administration of the scale takes between 3 and 15 min.

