### Participant timeline

Clinicians will be asked to draw up a list of patients who have presented self-injurious behavior in the last month. With this list, the patients will be identified on the days that they attend the control by their psychiatrist or psychologist of each Service. After the usual control of the patient, one of the members of the research group will explain the purpose of the study to the participant and legal guardian. Next, the researcher will give them a copy of the consent and/or assent to read carefully and invite them to participate in the study. After the invitation, those who agree to participate will be scheduled for a 30-min interview with one of the research group members.

The first interview will be face-to-face and it will determine if the participant meets the inclusion criteria and sign the informed consent. Then, a series of clinical and demographic data will be requested and the Spanish version of the Self-Injurious Thoughts and Behaviors Interview (SITBI) and the Difficulties in Emotion Regulation Scale (DERS) will be administered. At the end of the interview, the follow up interviews will be scheduled and those patients randomized to the intervention group will have the application downloaded to their cell phones. In addition, they will be given a brief 5 to 10-min tutorial on how the app works, they will be given written material on its functioning, and they will be directed to the website where there will be explanatory material.^1^

Follow-up interviews (day-30 and day-60): those will be conducted *via* video call according to the epidemiological context of the COVID-19 pandemic. During these calls, only the SITBI will be administered and participants will be asked if they have had any hospitalization due to suicidal behavior in that period, and if so, the date of admission. In the intervention group, to guarantee engagement with the CALMA app, the rater will explore whether or not the participant has used the application. In case of not using it, the obstacles and the alternatives to overcome them will be determined through a brief protocol (DBT missing links strategy) to reinforce the use of the application during the next evaluation period. At the same time, the technical team will work throughout the study to guarantee the proper functioning of the app.

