The final interview (day-90) will be face-to-face or by video call depending on the epidemiological context of the COVID-19 pandemic. The SITBI, the DERS and, to those who received the app, the User Experience Questionnaire short version (UEQ-s) and a series of questions related to the opinion about the app will be administered. At the end of this interview, we will obtain data from the patient about the frequency of use of the app (subjective use report) and our information technology team will also obtain data on the use of the different functionalities of the app from each participant (objective use report). A flowchart describing how an individual participant will progress through the phases of the research process is outlined in Figure 6.

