### Sample size

The sample size was calculated using the G*Power 3.1.9.4 statistical software according to the main objective. Considering a confidence level of 95%, a power of 80% and an effect size *d* = 0.85, 25 individuals per group are needed to detect a significant difference in the median frequency of self-injurious behaviors with the two tailed Mann–Whitney U test. Assuming a proportion of lost in the follow-up of 15%, then the study would have to start with 29 individuals per group.

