### Statistical analysis

To describe the sociodemographic characteristics of the patients in the two groups, absolute and relative frequencies (%) will be used for the qualitative variables, and the mean and standard deviation will be used for the only quantitative variable (age) if it presents a normal distribution according to the Shapiro–Wilk test. In case of presenting a non-normal distribution, the median and the interquartile range will be computed.

To compare the sociodemographic characteristics between the groups, the chi-square or Fisher’s exact test will be used for the qualitative variables, and the student’s t-test or the Mann–Whitney U test will be computed for the quantitative variable.

For all patients and at each follow-up moments, the difference between the frequency of each suicidal behavior and the baseline frequency will be calculated. Then it will be evaluated if these differences follow a normal distribution (Shapiro–Wilk test). In this case, the mean differences for each behavior between both groups will be compared using the t-Student test. Otherwise, the medians will be compared with the Mann–Whitney U test. The *p*-values obtained will be corrected according to the Bonferroni criterion.

To assess whether the change in emotional regulation mediates the change in the frequencies of each suicidal behavior, the difference between the value of the DERS scale at the last follow-up and the baseline will be calculated, and the Sobel test will be used on a regression model whose dependent variable will be the difference in the frequency of each behavior and the independent variable will be the treatment. Previously, the probability distribution of the quantitative variables will be evaluated and it will be considered whether it is necessary to carry out any transformation of data to guarantee compliance with the assumptions of the regression model.

Both for the frequencies of the different suicidal behaviors and for the DERS scale, the missing values will be imputed according with the multiple imputation method using chained equations (MICE) with appropriate models for each variable to be imputed, considering sociodemographic characteristics, the hospital of recruitment and the baseline measurements of frequencies and DERS scale as independent variables.

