Regarding acceptability, the UEQ Data Analysis Tool offers a benchmark to classify the application in 5 categories of 6 scales: excellent, good, above average, below average and bad allowing conclusions to be drawn about the relative quality of CALMA compared to other products.^2^

To evaluate and compare the time to readmission in patients enrolled during hospitalization, a Cox regression model will be adjusted, considering the treatment of each patient as the independent variable. For this, the time elapsed from study entry to readmission (event) or to loss of follow-up or final of the study (censoring) will be calculated. In all cases, a value of *p* less than 0.05 will be considered significant. Statistical analysis will be performed with RStudio 1.4.1106.

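### Time to psychiatric admission relies on the participant's own report and is censored at loss to follow-up, and four sections describe the event differently

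*Protocol article*

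**What the plan says.** All references are to the Protocol article.

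- **Source of the outcome.** Under Time to psychiatric admission, at the follow-up and final interviews "participants will be asked if they have had a psychiatric hospitalization for a self-injurious behavior during the follow-up period". Under Participant timeline, at day 30 and day 60 "participants will be asked if they have had any hospitalization due to suicidal behavior in that period, and if so, the date of admission". Neither section names a second source.
- **Analysis.** Under Statistical analysis, a Cox model runs from study entry to readmission, or "to loss of follow-up or final of the study (censoring"). It is described for participants who were in hospital when they enrolled.
- **Expected loss.** Under Sample size: "Assuming a proportion of lost in the follow-up of 15" per cent, giving 29 per group.
- **Contact with the services.** Under Subjects: "The participant must have plans to continue treatment in the next 3 months". The Safety procedure section describes a research collaborator at each recruitment centre and sends at-risk participants to that centre's emergency department.
- **Engagement support.** Under Participant timeline, the day-30 and day-60 calls explore app use in the intervention arm and work through obstacles to it. The control arm has no counterpart.

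**The concern.** A participant who stops attending can no longer report an admission, and the Cox model then treats that person as having the same future risk as those still followed. That is a weak assumption here. Everyone enrolled has self-injured in the previous month, and the article itself calls the participants high-risk. The Data management section also allows withdrawal after a serious adverse event that is attributable to the study or prevents participation, so loss can be tied to the outcome.

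Retention may also differ by arm, because only the app arm receives engagement support during the calls.

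A second problem compounds this. Whether an admission counts depends on the reason the participant gives for it, in a trial where participants know whether they have the app and the interviewer asks app users about it. That reason is worded differently from section to section. At stake are a named secondary comparison and part of the safety picture for 29 app users.

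**Working it through.** **1. The sections side by side**

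| Section | Event | Who is covered |
|---|---|---|
| Secondary specific objectives | Psychiatric admission, no reason required | Enrolled participants, by arm |
| Time to psychiatric admission | Psychiatric hospitalization for self-injurious behavior | Participants, by arm |
| Participant timeline (day 30, day 60) | Any hospitalization due to suicidal behavior | All interviewed |
| Statistical analysis | Readmission | Only those enrolled while inpatients |

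An admission for depression without self-injury counts under Secondary specific objectives but not under Time to psychiatric admission. An admission after non-suicidal cutting counts under Time to psychiatric admission and may not count under Participant timeline, depending on how broadly the participant understands suicidal behavior. An admission in someone enrolled as an outpatient counts under Secondary specific objectives and is outside the model in Statistical analysis.

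**2. The article's own loss figure**

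Inputs from Sample size: 25 evaluable per group, 15% loss, 29 enrolled per group. 25 × 1.15 = 28.75, which rounds up to the stated 29 (25 / 0.85 = 29.4 would give 30). The sample size is not in dispute here. Expected loss is 29 × 0.15 = 4.35 per arm, or 58 × 0.15 = 8.7 in total, about 9 people.

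**3. Share of admissions not seen**

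Let p be the admission risk in those followed and q the risk in those lost. The article gives neither, so both are assumptions.

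Share unseen = 0.15q / (0.85p + 0.15q)

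| p | q = p | q = 50% | q = 100% |
|---|---|---|---|
| 10% | 15% | 47% | 64% |
| 20% | 15% | 31% | 47% |
| 30% | 15% | 23% | 37% |

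For example, p = 20% and q = 50% gives 0.075 / (0.170 + 0.075) = 0.306. The q = p column is non-informative loss, which costs events but does not bias a Cox model.

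**4. Effect on the arm comparison**

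Take 29 per arm, p = 20% in both, so the observed risk ratio is 1.0.

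- 4 lost in each arm, equal risk among the lost: the true ratio stays 1.0.
- 2 lost on the app, 6 on control: observed events are 27 × 0.2 = 5.4 and 23 × 0.2 = 4.6. If half the lost were admitted, (5.4 + 1) / (4.6 + 3) = 0.84. If all were, (5.4 + 2) / (4.6 + 6) = 0.70.
- 6 lost on the app, 2 on control: 7.6 / 6.4 = 1.19 and 10.6 / 7.4 = 1.43.

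These figures are simple risks, not hazard ratios. Steps 3 and 4 assume that no lost participant had reported an admission before leaving, which overstates the effect because some would have done so at day 30 or day 60. They also use all 58 participants, whereas the Cox model as written covers an unstated subset.

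**The case against.** The strongest reply is that a journal article condenses a fuller protocol. Tracing of missed visits, use of records and rules for death may be set out there, and their absence here is not an error. That stands for anything inferred from silence. It does not remove the point, because the article does state its method: ask the participant, take the date from the participant, censor at loss.

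Several stronger readings are tempting, and the documents do not support them.

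- **That someone who dies would be given an imputed frequency.** The article says of behaviour frequencies and the emotion-regulation scale that "the missing values will be imputed according with the multiple imputation method using chained equations (MICE"), but it does not mention death. A rule may exist elsewhere.
- **That the recruiting hospitals hold all the facts.** They would know of their own admissions and emergency visits. Nothing shows that they know of admissions elsewhere or deaths outside hospital.
- **That records could repair the primary outcome.** "Suicidal behavior will be assessed using the Spanish version of the Self-Injurious Thoughts and Behaviors Interview (SITBI"), and counts of non-suicidal self-injury are largely known only by self-report. An interview is a reasonable source for them.
- **That being in hospital makes a participant missing.** Day-30 and day-60 interviews are by video call, "The final interview (day-90) will be face-to-face or by video call depending on the epidemiological context of the COVID-19 pandemic", and an admission can be reported with its date at a later interview.
- **That the trial is blind to safety events.** A suicide safety assessment takes place at every interview, with alerts to the site collaborator and the emergency physician. The article does not say that this information feeds the admission outcome.

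It is also fair to say that restricting the event to self-injury admissions is a legitimate choice. The difficulty is that the article does not make that choice consistently.

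**Conclusion.** The point holds for time to psychiatric admission. As written, admissions after the last attended interview are missed, and the event and analysis population differ between sections. The inconsistency is a matter of text and needs no assumption.

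The numerical effect is unknown. The only figure the article supplies is the 15% loss, about 9 of 58 people. With an assumed 20% admission risk in those followed, 15% to 47% of admissions would go unseen as risk among the lost rises from 20% to 100%. The low end is lost precision only. Bias between arms requires loss, or risk among the lost, to differ by arm. The one-sided engagement support makes that plausible, but the documents do not show that it will happen or in which direction.

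**What to change.** - **Time to psychiatric admission and Participant timeline:** for every randomised participant in both arms, whether or not interviews were attended, have the existing site collaborator check the recruiting service's records at day 90 for psychiatric admissions, their dates and known vital status. Ask the guardian whenever a visit is missed.
- **Event definition:** record all psychiatric admissions, with the reason as a separate field. A self-injury-specific analysis can then be derived without relying on the participant's attribution alone.
- **Consistency:** use one event and one population in Secondary specific objectives, Time to psychiatric admission, Participant timeline and Statistical analysis. If the inpatient-only readmission analysis is wanted, label it as a subgroup.
- **Statistical analysis:** censor at the last date on which admission status is known from interview or records. Report any deaths by arm, and do not impute behaviour frequencies after death. Whether death is a competing event or part of a composite is a separate choice; either is defensible if stated.

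The cost is a record check for 58 people at two hospitals and possibly a consent or ethics amendment. Admissions to other hospitals would still depend on the participant or guardian, and the self-injury frequency would remain self-reported.

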##### Sociodemographic variables

Sociodemographic variables are: age, sex, gender, sexual orientation, education level and treatment modality (outpatient/inpatient).

### Participant timeline

Clinicians will be asked to draw up a list of patients who have presented self-injurious behavior in the last month. With this list, the patients will be identified on the days that they attend the control by their psychiatrist or psychologist of each Service. After the usual control of the patient, one of the members of the research group will explain the purpose of the study to the participant and legal guardian. Next, the researcher will give them a copy of the consent and/or assent to read carefully and invite them to participate in the study. After the invitation, those who agree to participate will be scheduled for a 30-min interview with one of the research group members.

The first interview will be face-to-face and it will determine if the participant meets the inclusion criteria and sign the informed consent. Then, a series of clinical and demographic data will be requested and the Spanish version of the Self-Injurious Thoughts and Behaviors Interview (SITBI) and the Difficulties in Emotion Regulation Scale (DERS) will be administered. At the end of the interview, the follow up interviews will be scheduled and those patients randomized to the intervention group will have the application downloaded to their cell phones. In addition, they will be given a brief 5 to 10-min tutorial on how the app works, they will be given written material on its functioning, and they will be directed to the website where there will be explanatory material.^1^

Follow-up interviews (day-30 and day-60): those will be conducted *via* video call according to the epidemiological context of the COVID-19 pandemic. During these calls, only the SITBI will be administered and participants will be asked if they have had any hospitalization due to suicidal behavior in that period, and if so, the date of admission. In the intervention group, to guarantee engagement with the CALMA app, the rater will explore whether or not the participant has used the application. In case of not using it, the obstacles and the alternatives to overcome them will be determined through a brief protocol (DBT missing links strategy) to reinforce the use of the application during the next evaluation period. At the same time, the technical team will work throughout the study to guarantee the proper functioning of the app.

The final interview (day-90) will be face-to-face or by video call depending on the epidemiological context of the COVID-19 pandemic. The SITBI, the DERS and, to those who received the app, the User Experience Questionnaire short version (UEQ-s) and a series of questions related to the opinion about the app will be administered. At the end of this interview, we will obtain data from the patient about the frequency of use of the app (subjective use report) and our information technology team will also obtain data on the use of the different functionalities of the app from each participant (objective use report). A flowchart describing how an individual participant will progress through the phases of the research process is outlined in Figure 6.

